### Outcome measurements

The PSQI-K and ISI-K are evaluated to confirm the effect of KGT granules on insomnia in the elderly. This will be measured three times: before taking the investigational drug, at the end of 12 weeks of medication, and after 12 weeks of 12-week medication.

To evaluate cognitive function, the SNSB-D is measured twice: at screening and at the end of 12 weeks of medication. In addition, to evaluate quality of life, SF-36 is measured three times: before taking the investigational drug, at the end of 12 weeks of medication, and after 12 weeks of the 12-week medication. The S-GDS, which evaluates depression, is measured twice in total: before taking the investigational drug and at the end of 12 weeks of medication.

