#### Efficacy analysis

Efficacy evaluation is based on the FAS analysis group, and efficacy is analyzed and presented with reference to the PP analysis group. For safety evaluation, the ITT analysis group is the main assay.

Analysis of primary efficacy endpoints.

Participants with PSQI-K scores before the study and at least once after consuming the investigational product are analyzed. Based on the baseline, the difference between the two groups in the total PSQI-K score change at weeks 12 and 24 is analyzed using repeated measures analysis of variance (RM ANOVA) and linear mixed model (LMM) methods.

2)Analysis of secondary endpoints.

The PSQI-K score change will be analyzed by a paired t-test within each group for changes at 12 and 24 weeks based on the baseline. The ISI-K score change will be analyzed using the paired t-test within each group and the independent t-test between the two groups at the 12-week dosing period and at 24 weeks based on the baseline. The SNSB-D and S-GDS score changes will be analyzed using the paired t-test within each group and the independent t-test between the two groups with respect to the score change at week 12, based on the baseline. The SF-36 score change will be analyzed using a paired t-test within each group and an independent t-test between the two groups at 12 and 24 weeks based on the baseline. Changes over time will be analyzed using the RM ANOVA and LMM methods. The estimated values of the mean difference between the groups, 95% confidence intervals, and p-values will be presented.

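### Secondary scales are compared between arms by t-tests on raw change, although the baselines that would sharpen the comparison are already collected

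*Protocol article*

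**What the plan says.** The protocol article, under Efficacy analysis, names the between-group test for each secondary scale:

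- SNSB-D and S-GDS: "independent t-test between the two groups with respect to the score change at week 12, based on the baseline".
- ISI-K: "independent t-test between the two groups at the 12-week dosing period and at 24 weeks based on the baseline".
- SF-36: "an independent t-test between the two groups at 12 and 24 weeks based on the baseline".

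In these sentences the reference to baseline defines the change score. It does not make baseline a covariate, and neither ANCOVA nor a baseline covariate appears anywhere in the article. The section adds, without model terms: "Changes over time will be analyzed using the RM ANOVA and LMM methods".

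The baselines exist. Under Outcome measurements, "the SNSB-D is measured twice: at screening and at the end of 12 weeks of medication", and the S-GDS "is measured twice in total: before taking the investigational drug and at the end of 12 weeks of medication". ISI-K and SF-36 are measured before dosing, at week 12 and at week 24.

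For the primary endpoint the article says that "the difference between the two groups in the total PSQI-K score change at weeks 12 and 24 is analyzed using repeated measures analysis of variance" and by an LMM. The terms of that model are not listed.

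**The concern.** Subtracting the baseline is not the same as adjusting for it. When baseline and follow-up correlate imperfectly, the arm that happens to start worse tends to show the larger improvement, and a t-test on change counts that excess as part of the treatment difference. ANCOVA estimates from the data how much of the baseline difference carries forward and removes that much.

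The article plans 30 per arm on a central-limit argument, with no effect size, SD or power, so nothing shows that there is precision to spare. Allocation is by 1:1 blocks, and no stratification by a baseline score is stated. At stake are wider intervals than necessary on the secondary scales, and estimates that depend on the luck of the baseline draw.

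**Working it through.** **The plan's own figure.** The 30 per group cannot be reproduced as a power calculation, because the inputs for one are not given. For orientation, at two-sided 5% and 80% power the detectable difference is (1.960 + 0.842) × √(2/30) = 0.72 SD of whatever variable is analysed.

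**Inputs.** From the article: n = 30 per arm, 1:1 allocation, two-sided 5%. Assumed, because the article does not give them: the baseline-to-follow-up correlation ρ (0.3 to 0.9), equal baseline and follow-up SDs in the main table, and a true difference of 0.5 SD for the power columns.

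**Precision.** Let s0 and s1 be the baseline and follow-up SDs.

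- Variance of change: s0² + s1² − 2ρ·s0·s1
- ANCOVA residual variance: s1²(1 − ρ²)
- Difference between them: (s0 − ρ·s1)², which is never negative

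With s0 = s1 the ratio of ANCOVA to change variance is (1 − ρ²) / [2(1 − ρ)] = (1 + ρ)/2. Estimating the slope multiplies the ANCOVA variance by 1 + 1/(2n − 4) = 1 + 1/56 = 1.018.

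**Imbalance.** The SE of the baseline difference between arms is √(2/30) = 0.26 SD. With equal SDs the change-score estimate shifts by −(1 − ρ) times the realised baseline difference; the ANCOVA estimate does not shift. The last column gives the size of the shift for a one-SE imbalance.

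| ρ | Variance ratio (1+ρ)/2 | With slope cost | Power, change t-test | Power, ANCOVA | Shift, SD |
|---|---|---|---|---|---|
| 0.3 | 0.65 | 0.66 | 36% | 51% | 0.18 |
| 0.5 | 0.75 | 0.76 | 48% | 59% | 0.13 |
| 0.7 | 0.85 | 0.87 | 69% | 75% | 0.08 |
| 0.8 | 0.90 | 0.92 | 85% | 88% | 0.05 |
| 0.9 | 0.95 | 0.97 | 98.9% | 99.1% | 0.03 |

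Power is from the noncentral t with 58 and 57 degrees of freedom. Simulation with 20,000 trials at each of ρ = 0.3, 0.5, 0.7 and 0.9 gave variance ratios of 0.667, 0.758, 0.867 and 0.968, and shifts of −0.70, −0.51, −0.30 and −0.10 per unit of baseline difference (about 0 for ANCOVA). Both estimators averaged −0.50 for a true −0.50.

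**Unequal SDs.** At ρ = 0.5 and s1 = 1, the ANCOVA residual variance is 0.75. Before the slope cost:

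| s0/s1 | Variance of change | Ratio |
|---|---|---|
| 1.0 | 1 + 1 − 1 = 1.00 | 0.75 |
| 0.85 | 0.7225 + 1 − 0.85 = 0.8725 | 0.86 |
| 0.7 | 0.49 + 1 − 0.70 = 0.79 | 0.95 |
| 0.5 | 0.25 + 1 − 0.50 = 0.75 | 1.00 |

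The gain vanishes where s0 = ρ·s1. There ANCOVA loses only the slope cost, about 1.8%.

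**Does the planned RM ANOVA or LMM already adjust?** SNSB-D and S-GDS have one post-baseline measurement. With two time points, the group-by-time test in RM ANOVA is the t-test on change, so it adds no adjustment. For ISI-K and SF-36 a mixed model could adjust, but its terms are not given and the t-test remains the named between-group comparison.

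**The case against.** - **The t-test is sound under randomization.** This stands. A reader might infer that the comparison is biased or that its type I error is wrong. The documents do not support that: averaged over allocations the change-score difference is unbiased, and the shift exists only given the imbalance that occurs.
- **The primary analysis may already adjust.** A reader might infer from "Based on the baseline, the difference between the two groups in the total PSQI-K score change at weeks 12 and 24 is analyzed" that the primary comparison is unadjusted. The article names an LMM without its terms, and covariates are commonly left to an analysis plan that is not shown. No firm criticism of the primary analysis follows.
- **The gain may be small.** This stands in part. It is tempting to say that change scores lose precision whenever the correlation is below 1, but that needs equal SDs and ignores the slope cost. Entry requires an ISI-K score above 8 and excludes dementia and mild cognitive impairment, so baseline ISI-K and SNSB-D may be less spread out than at follow-up. A stable cognitive battery could also have ρ of 0.8 to 0.9, where the saving is about 8% to 3%.
- **Mixed models and intervals are already planned.** The article does promise mean differences with 95% confidence intervals. But it specifies t-tests on change as the comparison of arms, and that is a stated choice rather than a gap.
- **Enrolment has begun.** Eight subjects were enrolled by the article's status report, and changes to the study need IRB approval. This adds an administrative step and leaves the statistical case unchanged.

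**Conclusion.** The point holds for the stated secondary t-tests on ISI-K, SNSB-D, S-GDS and SF-36. It is a fault of efficiency and robustness, not of validity. With 30 per arm and equal SDs, baseline adjustment cuts the variance by about 34% at ρ = 0.3, 24% at 0.5, 13% at 0.7, 8% at 0.8 and 3% at 0.9. Fewer completers would raise the slope cost slightly. The size rests on correlations and SDs that the document does not give, and a moderately narrower baseline SD reduces it, to nothing at s0 = ρ·s1. The direction does not rest on them: apart from one estimated slope, ANCOVA cannot be less precise. For the primary PSQI-K model only a consistency recommendation applies.

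**What to change.** Replace each between-group t-test on change as follows:

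- **SNSB-D and S-GDS:** ANCOVA of the week-12 score on treatment, with the same scale's baseline as covariate.
- **ISI-K and SF-36:** an LMM with treatment, visit, treatment-by-visit and the score's own baseline, reporting the week-12 and week-24 treatment contrasts.
- **All four:** give the adjusted mean difference with its 95% confidence interval.
- **PSQI-K:** for consistency, state the terms of the primary LMM and include baseline PSQI-K as a covariate.

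The cost is one degree of freedom per model and a wording amendment, with IRB approval where required. No new data are needed. The change should be dated before unblinding, so that the adjustment cannot appear to have been chosen on the results.

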#### Adverse events

An adverse event is a symptom that was not observed before the administration of the investigational drug, which is a new symptom during the dosing period. This is a generic term for temporary phenomena related to the administration of investigational drugs. Events (symptoms, onset date, duration, etc.) expected to be adverse events of the investigational drug should be recorded in the adverse event report. The severity of adverse events is evaluated according to the severity of symptoms, by referring to the evaluation criteria of the investigator. A degree that does not interfere with normal daily activities (functions) to such an extent that the participant hardly notices it or the degree to which most of them do not require treatment is evaluated as mild. If the participant feels discomfort to a degree that interferes with normal daily life (function) or the participant is deemed to continue the study but may require treatment, it is evaluated as moderate. The degree to which daily life (function) is impossible because the participant is very uncomfortable, or to a degree that continuous study participation is deemed impossible, such that treatment or hospitalization may be required, is evaluated as severe. The responsibility of providing medical care to the injured participant lies with the principal investigator.

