**Methods:**

In this single-center, double-blind, randomized controlled trial, 60 older adults with insomnia and subjective cognitive decline will be recruited and randomly assigned to the KGT or placebo group. The KGT group will take KGT granules thrice a day for 12 weeks, whereas the control group will take placebo granules in the same manner.

Participants will be assessed for sleep, cognitive function, quality of life, and depression using the Pittsburgh Sleep Quality Index-Korean (PSQI-K), Insomnia Severity Index-Korean (ISI-K), Seoul Neuropsychological Screening Battery–Dement (SNSB-D), 36-item MOS Short Form Survey (SF-36) and Short version of the Geriatric Depression Scale (S-GDS) before and at the end of administration of the investigational product. The PSQI-K, ISI-K, and SF-36 will be further assessed 12 weeks after the end of medication to determine whether the effects on sleep and quality of life are sustained. The PSQI-K total score difference between the two groups at 12 and 24 weeks will be the primary outcome; all other endpoints will be secondary.

Safety will be assessed by performing blood tests and electrocardiograms before taking the investigational drug, 6 weeks after taking the drug, and 12 weeks after taking the drug; any adverse events will be observed throughout the study.

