### Safety assessments and monitoring

Adverse events will be investigated during each visit. Subjects who took the investigational drug at least once are eligible for safety analysis. Any undesirable medical findings indicating symptoms not observed prior to the study are considered adverse events.

At every visit, blood pressure, pulse rate, and body temperature are investigated to determine the participants’ health status. Laboratory tests for glucose, aspartate aminotransferase (AST), alanine aminotransferase (ALT), blood urea nitrogen (BUN), creatinine, sodium, potassium, chloride, lactate dehydrogenase (LDH), creatine phosphokinase (CPK), and electrocardiography (ECG) are investigated before taking the investigational drug and after 6 and 12 weeks of medication. Participants with abnormal laboratory test results should be followed up. Additionally, total cholesterol, HDL cholesterol, LDL cholesterol, triglyceride, homocysteine, T3, free T4, and thyroid stimulating hormone (TSH) levels are investigated at baseline.

After visit 1 (baseline), the investigators monitor status of medication, adverse events, and concomitant medications via phone calls once a week until the next visit. After the end of the medication at visit 3 (12 weeks), the investigators monitor adverse events and concomitant medications via phone call every two weeks until the final visit.

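### The protocol defines adverse events in two incompatible ways, one limited to new, temporary, drug-related symptoms during dosing, and it also names two different safety sets

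*Protocol article*

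**What the plan says.** Adverse events are defined in two places in the protocol article.

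- **Adverse events** (under Statistical analysis): an adverse event is a symptom absent before administration, "which is a new symptom during the dosing period. This is a generic term for temporary phenomena related to the administration of investigational drugs". The recording instruction follows: "Events (symptoms, onset date, duration, etc.) expected to be adverse events of the investigational drug should be recorded in the adverse event report". The section then grades severity as mild, moderate or severe.
- **Safety assessments and monitoring**: "Any undesirable medical findings indicating symptoms not observed prior to the study are considered adverse events". After dosing ends at week 12, "the investigators monitor adverse events and concomitant medications via phone call every two weeks until the final visit". The Abstract (Methods) agrees on the period: "any adverse events will be observed throughout the study".

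The population for the safety analysis is also given twice.

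- **Safety assessments and monitoring**: "Subjects who took the investigational drug at least once are eligible for safety analysis".
- **Efficacy analysis**: "For safety evaluation, the ITT analysis group is the main assay". The opening paragraph of Statistical analysis ties the ITT principle to everyone randomised, with no dosing condition.

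**The concern.** Efficacy and safety together form the primary aim stated in the Background. A harms comparison needs one rule for what is recorded, over what period and in whom. Here one text makes an event conditional on timing (during dosing), duration (temporary) and causality (related to the product), and the other does not. Site staff could reasonably follow the Adverse events section, because it alone carries a recording instruction and severity grades.

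A filter applied when events are recorded cannot be undone at analysis. An event never entered on the case report form cannot be recovered by an analysis plan, whatever that plan says. The denominator conflict is different: either set can be formed later from the data, so it is easier to repair and matters less.

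**Working it through.** The document gives no adverse-event rate and no safety power, so there is no stated figure to reproduce. The check compares the texts and then gives a rough idea of size.

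**1. The two definitions side by side**

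| Feature | Adverse events section | Safety assessments and monitoring, and Abstract |
|---|---|---|
| Period | Dosing period (weeks 0–12) | Monitored to the final visit (week 24) |
| Causality | Related to the product | No condition |
| Duration | Temporary | No condition |
| New symptoms | Yes | Yes: findings that indicate symptoms not seen before the study |
| Worsening of an existing condition | Not clearly covered | Not clearly covered |
| Symptom-free laboratory or ECG change | Not clearly covered | Not clearly covered as an event; abnormal laboratory results are followed up |

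The first three rows are contradictions. The last two are gaps common to both texts.

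**2. Observation time outside the narrower definition**

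Inputs: 12 weeks of dosing (Intervention) and follow-up to week 24 (Statistical analysis). Share outside = (24 − 12)/24 = 50%. This is a share of time, all of it off product, and not a share of events.

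**3. What that could mean in participants (illustration)**

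Assume a constant weekly hazard h of a first event, the same on and off product, with h between 0.01 and 0.02. The share with at least one event by week t is 1 − exp(−h·t).

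- h = 0.01: week 12, 1 − exp(−0.12) = 11.3%; week 24, 1 − exp(−0.24) = 21.3%. Difference 10.0 percentage points, or about 3 of 30.
- h = 0.02: week 12, 1 − exp(−0.24) = 21.3%; week 24, 1 − exp(−0.48) = 38.1%. Difference 16.8 percentage points, or about 5 of 30.

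The planned size is 30 per group (Sample size), so each participant whose only event is not counted shifts that arm's proportion by 1/30 = 3.3 percentage points. The further loss of events judged unrelated cannot be sized from the document.

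**4. The denominator**

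Let k be the number per arm randomised but never dosed (assumed; the document reports none). The proportion on the dosed set exceeds that on all randomised by a relative 30/(30 − k) − 1.

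| k | Relative difference | Example with 6 participants affected |
|---|---|---|
| 0 | 0% | 6/30 = 20.0% on both |
| 1 | 3.4% | 6/30 = 20.0% against 6/29 = 20.7% |
| 2 | 7.1% | 6/30 = 20.0% against 6/28 = 21.4% |
| 3 | 11.1% | 6/30 = 20.0% against 6/27 = 22.2% |

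The second conflict is nil if everyone takes a dose and small otherwise.

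**The case against.** The strongest reply is that the protocol's operations point to full collection. Adverse events are asked about at every visit, by weekly call after baseline, and by call every two weeks after week 12. On that view the Adverse events section is loose wording. This stands in part: under-counting follows only if that section governs. The document does not say which text governs, so the rule remains undetermined.

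Several stronger readings are tempting, and the document does not support them.

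- **The safety comparison is already censored and has the wrong denominator.** Both parts are conditional: the first on the narrower definition governing, the second on someone being randomised and never dosed.
- **The calls after week 12 can yield no adverse event.** They could still pick up late-reported or continuing events that began during dosing.
- **Unexpected or lasting harms are excluded.** In "expected to be adverse events of the investigational drug should be recorded in the adverse event report", the word for expected may simply mean thought to be. Exclusion of lasting harm rests on one word, while the same section grades events that may need hospitalisation and the Drop-out criteria provide for serious events. A judgement of relatedness before recording remains on either reading.
- **Laboratory and ECG harms are lost.** Blood tests and ECG are safety assessments in their own right at baseline and weeks 6 and 12, and abnormal laboratory results are followed up. All these time points fall before dosing or within the dosing period, so the window conflict does not touch them. Only their status as adverse events is unclear, and that is so under both definitions.
- **The relatedness filter favours KGT.** Investigators, coordinators and pharmacists stay blind to the end of the study (Randomization, allocation concealment, and blinding). The judgement would be made without knowledge of arm, so it mainly loses events and need not favour either group.

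The primary outcome, the PSQI-K total score, is unaffected, and no formal between-arm test of adverse events is stated.

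**Conclusion.** The concern holds as an internal contradiction that leaves the adverse-event count undefined. If the Adverse events section governs, events starting in the 12 weeks after dosing and events judged unrelated drop out. Under the assumed hazards the first of these alone is about 10 to 17 percentage points of participants per arm. If that section does not govern, the reader cannot tell what is counted. The expected consequence is an under-count made blind to arm, not a tilt towards one product. Worsening of existing conditions and symptom-free test changes are a gap in both definitions.

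The safety-set conflict is real but minor: nil if all are dosed, and 3.4% to 11.1% relative if 1 to 3 of 30 per arm are not. The hazards and never-dosed counts are assumptions. The contradictions come from the text and do not depend on them. This should be fixed because safety is part of the primary aim and unrecorded events may not be recoverable, but it does not threaten the primary efficacy analysis.

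**What to change.** 1. Reconcile the Abstract, Safety assessments and monitoring, and Adverse events to one definition: any untoward medical occurrence from first dose to the week-24 visit, whether or not thought related to the product. State that it includes worsening of existing conditions and clinically significant laboratory or ECG changes.
2. Record causality as a separate item, judged blind to arm, and not as a condition for recording.
3. Report events during dosing and events after dosing separately, so that the off-product period does not obscure the on-product comparison.
4. Replace the ITT sentence for safety in Efficacy analysis with the set of participants who took at least one dose, as Safety assessments and monitoring already states.
5. Check the records of those already enrolled (eight as of 25 August 2023, per Trial status) for events left out under the narrower wording.

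The cost is a change to the protocol and case report form instructions, slightly more events to record, and a short review of existing records. Sample size, visits and the primary analysis do not change.

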## Discussion

Insomnia is a common symptom that can cause various physical and psychological problems [9], and it has been reported that one-third of the total American population suffers from sleep-associated complications [36]. A survey on the prevalence of insomnia symptoms in the elderly in Europe showed that the prevalence was variously investigated as 16.6% in Denmark and 32.1% in Poland [3]. A study using the National Health Insurance Service-National Sample Cohort (NHIS-NSC) from 2002 to 2013 in South Korea [37] reported that one in ten people over the age of 60 and one in five from the age of 80 years or older showed a significant increase in the number of patients with insomnia as they aged. The proportion of the population aged ≥ 65 years is expected to increase from 9.8% to 2022 to 20.1% in 2070 [38]; therefore, it is estimated that the number of elderly patients with insomnia will also increase.

Insomnia is more common in the elderly, as aging decreases deep sleep and leads to more frequent awakenings and a tendency to wake up earlier in the morning [39]. This leads to fatigue, disruption of daily activities, decreased quality of life, and increased depression [40, 41]. Additionally, sleep disorders can cause cognitive decline in older adults, worsening mild cognitive decline [42] or increasing the risk of Alzheimer’s disease (AD) [43]. Sleeping pills, a common treatment for older adults with insomnia, can cause cognitive decline. Older adults who reported taking sleeping pills had an increased risk of developing dementia 15 years later [13].

Seniors with sleep disorders experience discomfort owing to poor cognitive function, and the frequent use of sleeping pills to treat insomnia can also lead to cognitive decline. Therefore, there is a need for safe and effective treatments for older adults with insomnia without cognitive decline.

KGT is a traditional herbal prescription that has been widely used for insomnia, forgetfulness, and depression in East Asia. Therefore, it can be prescribed to older adults with insomnia who experience memory loss. A clinical study of patients with cancer with sleep disorders showed that KGT was effective [18]; however, no such studies have been reported in older patients with insomnia.

The memory-enhancing effects and mechanisms of KGT have been confirmed in several in vivo, in vitro, and clinical studies. KGT extended the survival period of mice injected with N-methyl-d-aspartic acid (NMDA) and showed a protective effect against delayed neuronal death in cornu ammonis 1 (CA1) pyramidal cells of the gerbil hippocampus [44]. In a study on age-induced learning performance impairment using senescence-accelerated mice (SAM), the retention rate in the step-through test increased, the number of errors in the step-down test decreased, and the conditioned avoidance response rate in the shuttle-box test increased in the group administered KGT. It has been objectively confirmed that KGT could improve learning ability in aging models, and the possibility of using KGT to treat cognitive decline due to aging has been suggested [45].

In a clinical study of 75 patients with AD in Japan, treatment with KGT for 3 months significantly improved the MMSE score compared to the control group, suggesting the potential for the clinical application of KGT in cognitive decline [46].

KGT also improved cognitive function in 30 patients with amnestic mild cognitive impairment (MCI) [19]. This preliminary study showed that 24 weeks of KGT administration in patients with amnestic MCI resulted in a significant improvement in the CDR-SB (Clinical Dementia Rating-Sum of Boxes) scores, whereas the scores worsened in the placebo group. Additionally, the total and memory domain scores of the Seoul Neuropsychological Battery (SNSB-D) were significantly improved in the KGT group compared to the placebo group, indicating that the overall cognitive function of the KGT group was significantly improved compared to the placebo group. This suggests the feasibility of using KGT in amnestic MCI patients with a high risk of progression to dementia.

Insomnia and cognitive decline are particularly important due to their negative effects such as reduced quality of life and high economic costs [47]. A meta-analysis showed that insomnia groups perform worse in various areas of cognitive functioning, such as working memory, episodic memory, and some executive functions [48], and chronic insomnia has been reported to cause atrophy of the CA1 subregion, leading to cognitive impairment [49]. After all, lack of sleep can affect future cognitive function; therefore, getting adequate sleep is crucial for maintaining cognitive function in older adults.

Elderly patients with insomnia experience cognitive decline due to insomnia; therefore, it is necessary to study whether prescriptions traditionally used for insomnia are effective in the elderly, considering their characteristics, such as cognitive decline.

We hypothesized that KGT would be effective and safe for improving sleep status, cognitive function, and quality of life in elderly individuals with insomnia and subjective cognitive decline. This clinical study will generate data suggesting the therapeutic efficacy of KGT in insomnia in older adults. If the results of this study prove the efficacy and safety of KGT, it will serve as a basis for further use in the elderly with insomnia and will also contribute to the prevention of memory decline due to insomnia in the long term.

The limitation of the study design is that the inclusion criteria included not only those who do not take sleeping pills but also those who take sleeping pills if there was no change in their medication. The study period can be extended if the recruitment period is prolonged, and any changes to the study, including termination, will be made after approval from the IRB.

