### Eligibility

#### Inclusion criteria

Participants who meet all the criteria below are eligible to participate:Those who complain of insomnia according to the criteria presented by DSM-5 > 65 years.Those with an Insomnia Severity Index Korean (ISI-K) score of > 8.Those with a Subjective Cognitive Decline Questionnaire (SCD-Q) score of > 7 and a Korean Dementia Screening Questionnaire-Cognition (KDSQ-C) score of < 6.Those who have not received any new treatments related to insomnia within the last 2 weeks: pharmacological and non-pharmacological treatments.Those who have not received cognitive-related drug treatments within the last 2 weeks.Cognitive-related drugs include cerebral function-improving agents, cerebral circulation-activating drugs, and other drugs or nutrients that can affect cognition.Those who have been in a stable state without any change in medications for underlying diseases for the past 4 weeks or more and who are planning to take stable medications during the study period.Those who have no problems with communication.Those who voluntarily decided to participate and signed the written consent form.

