### Concomitant medication

It can be allowed at the discretion of the investigators if it does not fall under the prohibited drug category among the drugs taken at least 2 weeks before participating in the study. Drugs used for the transient treatment of other diseases should be administered in consultation with the investigators. For all other drugs, information (product name, purpose of administration, duration, dosage, etc.) are recorded in a case report form.

Drugs and non-pharmacological treatments that may improve insomnia or affect cognitive function are prohibited. If the participants have taken these drugs or received treatment during the medication period, the study will be discontinued.

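### The Concomitant medication section prohibits, and discontinues for, the stable sleeping-pill use that the inclusion criteria allow

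*Protocol article*

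**What the plan says.** Two places in the protocol article admit people who already take a sleeping pill.

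- Discussion, limitation paragraph: the inclusion criteria cover people who take no sleeping pills, "but also those who take sleeping pills if there was no change in their medication".
- Inclusion criteria, insomnia treatment: "Those who have not received any new treatments related to insomnia within the last 2 weeks". Only new treatment is barred; continuing treatment is not.

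The Concomitant medication section sets a different rule in three steps.

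- Drugs already in use before entry may continue at the investigators' discretion, but only "if it does not fall under the prohibited drug category among the drugs taken at least 2 weeks before participating in the study".
- The prohibited category is broad: "Drugs and non-pharmacological treatments that may improve insomnia or affect cognitive function are prohibited".
- The consequence is "If the participants have taken these drugs or received treatment during the medication period, the study will be discontinued". I read this as the end of that participant's own participation.

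The Drop-out criteria remove a participant for taking drugs that could affect the results only when the investigators have not instructed or agreed to it.

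**The concern.** A sleeping pill is a drug that may improve insomnia. Someone who enters on an unchanged pill and keeps taking it, as the Discussion envisages, breaks the Concomitant medication rule from the first day of study product. Site staff then have one text that enrols this person and another that discontinues the same person.

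Participants could be lost for a reason unrelated to the treatment or to their own conduct, and their primary outcome could be lost with them. Sleep medication use is also one of the seven scored PSQI-K components (Primary outcome), so the unsettled rule touches the endpoint itself.

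**Working it through.** No figure in the plan is in dispute, so the check is to follow one participant through the rules: an older adult with insomnia on a long-standing, unchanged sleeping pill who meets the other criteria.

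1. **Entry.** The insomnia-treatment criterion is met because the pill is not new. The Discussion confirms that admitting such a person is intended.

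2. **Does Concomitant medication exempt earlier use?** No. Its opening sentence deals with drugs taken before entry and allows them only outside the prohibited category. The next paragraph puts anything that may improve insomnia inside that category. Reading the prohibition as covering only newly started drugs does not fit the opening sentence.

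3. **During the 12 weeks.** Taking the pill triggers discontinuation. Under Safety assessments and monitoring, concomitant medications are checked by weekly phone call after baseline, so continued use would surface early.

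4. **Drop-out criteria.** A pill that the investigators know of and accept does not meet the drop-out trigger. That agrees with the Discussion and leaves Concomitant medication as the outlier.

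5. **Effect on the primary analysis.** Under Outcome measurements, PSQI-K is taken before treatment, at week 12 and at week 24. Under Efficacy analysis, the primary analysis needs a baseline score and at least one score after starting product. A participant dropped before week 12 and not followed further has no such score.

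6. **Effect on the per-protocol set.** Under Statistical analysis, membership requires 12 weeks of product and follow-up to week 24. A participant discontinued during treatment cannot meet this.

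7. **Size per case.** The planned size is 30 per group (Sample size), so each loss is 1/30 = 3.3% of an arm. The sleep-medication component scores 0 to 3 of a possible 21 points.

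The article gives no count or expected share of sleeping-pill users, so the total loss cannot be computed.

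**The case against.** The best defence is that most of the document is coherent. The insomnia-treatment criterion, the Discussion and the drop-out rule all fit one policy: stable use is admitted, and unauthorised use is not. The article does not itemise the prohibited drugs, and the full protocol may do so and may exempt stable pills. Admitting stable users is also a choice the sponsor openly lists as a limitation.

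Much of that stands. It shows which text is the outlier, and the choice to admit stable users is not itself criticised here. But condensing a protocol can explain a missing list; it does not explain two incompatible rules that are both stated. If stable pills are exempt in the full protocol, Concomitant medication states the rule wrongly. If they are not, the Discussion does.

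A reader might infer more than the text supports:

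- **That the two stability windows conflict.** The 2-week limit concerns new insomnia treatment. The other criterion, "without any change in medications for underlying diseases for the past 4 weeks or more", concerns different drugs. All inclusion criteria must be met, so the two are cumulative.
- **That the cognition-drug criterion bars sleeping pills.** It reads "Those who have not received cognitive-related drug treatments within the last 2 weeks", and its definition ends with "other drugs or nutrients that can affect cognition". The items it names are agents given for cerebral function or circulation. Bringing hypnotics in means stretching that last phrase with a background remark in the Discussion about cognitive harm from sleeping pills.
- **That the psychotropic-drug exclusion bars them.** The article does not say whether hypnotics count as psychotropic.

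The last two are worth a line of clarification but are not shown to be contradictions.

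**Conclusion.** The concern holds as a conflict between Concomitant medication on one side and the Discussion and the insomnia-treatment criterion on the other. Applied as written, Concomitant medication discontinues stable sleeping-pill users whom the inclusion criteria admit. That can cost them their week-12 PSQI-K and does cost them per-protocol membership.

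The conclusion assumes that a sleeping pill is a drug that may improve insomnia and that the discontinuation sentence refers to the individual participant. Loss of the primary outcome further assumes that a discontinued participant is dropped before week 12 and not assessed afterwards.

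The number affected is unknown and may be zero, either because few users enrol or because other criteria are applied so as to screen them out. A reader might infer that the primary comparison is biased. The documents do not support that: nothing indicates that the rule would fall more heavily on one arm, and participants and investigators are blinded. What is shown is avoidable loss from a small trial and an unclear study population. It should be fixed, and the fix is small.

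**What to change.** Add one exemption to Concomitant medication, for example: *Sleeping pills in use and unchanged before entry, as allowed by the inclusion criteria, and kept unchanged during the study are permitted and recorded; new or changed insomnia treatments are prohibited and lead to discontinuation.* This relies on the existing inclusion criteria and introduces no new time window. In the same amendment, confirm that the psychotropic-drug exclusion and the cognition-drug criterion are not meant to bar these users.

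If the sponsor does not want sleeping-pill users, exclude them explicitly at screening, so that none is randomised and then removed, and delete the sentence in the Discussion.

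Under either option, check the medication records of participants already enrolled (eight of the planned 60 at 25 August 2023, under Trial status) against the chosen rule. The cost is an IRB-approved wording amendment and that record check. No extra visit, measurement or participant is needed.
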